### 2.5. Blinding

Participants and personnel responsible for delivering the physical activity intervention will not be blinded due to the nature of the intervention, as they will become aware of their group allocation. However, the data analysts and evaluators will be blinded to group allocation to minimize bias in assessment and analysis bias. Group assignments will be coded as A or B in all data collection forms and databases, without revealing which code corresponds to the intervention or control group.

Unblinding will only be permissible in exceptional circumstances, such as a medical emergency requiring knowledge of the participant’s assigned group. In such cases, the IP for generating the allocation sequence will reveal the assignment following a documented procedure, and the reason for unblinding will be recorded.

### 2.6. Ethical Approval

The study protocol was approved by the Research Ethics Committee of the University of Extremadura (approval reference: 55/2021). The trial was registered in the Open Science Framework (OSF) under the title Cost-effectiveness of Autonomous Smart Insole–based physical exercise on brain, motor pattern and quality of life in FM (AUSIEX) (registration identifier: https://doi.org/10.17605/OSF.IO/Q6GZ4 on 3 June 2025. Participants will receive a detailed explanation of the procedures and will be provided written informed consent, following the principles outlined in the Declaration of Helsinki.

### 2.7. Procedures

Figure 1 illustrates the study timeline and the sequence of the interventions. Initially, anthropometric measurements will be obtained to calculate participants’ body mass index (BMI). Subsequently, participants will provide sociodemographic information and will complete the following questionnaires: the International Physical Activity Questionnaire (IPAQ); the FM Impact Questionnaire-Revised (FIQ-R); the Falls of Efficacy Scale International (FES-I); the EuroQol 5 dimensions-5 levels (EQ-5D-5L); and the EQ-Health and Wellbeing (EQ-HWB and EQ-HWB-9).

Pre-intervention and post-intervention assessments: On the first day, after completing the questionnaires, participants will undergo a cognitive assessment using the Montreal Cognitive Assessment (MoCA). This will be followed by the physical (strength and mobility test) and cognitive task, which will be administered under both single-task and dual-task conditions. On the second day, the following assessments will be conducted: (1) a 5-min baseline resting EEG, (2) Stimulus–Response (S-R) paradigm, and (3) physical performance tasks, including balance and agility gait tests.

All physical performance and outcome assessments will be conducted by evaluators blinded to participants’ group allocation, as described in Section 2.4.

### 2.8. Intervention

Participants in the exercise group will take part in a six-week physical exercise training program, while those in the control group will continue their usual daily routines. The exercise group will be submitted to an intervention consisting of two group-based sessions per week, lasting 60 min, with a maximum of ten participants per group. Sessions will be held in facilities provided by the collaborating FM associations or University of Extremadura. The program will focus on balance, postural control, coordination, mobility, aerobic conditioning, and strengthening of both upper and lower limbs, with particular emphasis on the practice and learning compensatory stepping strategies [24] through creative movement. The proposed exercises are specifically designed to encourage adaptive stepping responses to balance challenges, promoting effective motor strategies to regain stability under dynamic and potentially destabilizing situations. All sessions will be supervised by a qualified physical exercise professional with a degree in Physical Activity and Sport Sciences and a Master’s degree in Health. The trainer will have at least five years of experience working with special groups, specifically individuals with FM, and will provide continuous technical feedback to ensure the correct execution of movements.

Each session will be divided into two parts of 30 min. The first part will include the strength training exercise and the second the creative dance training, based on the fundamental components of creative dance [25]. A typical session will include five to ten min of warm-up exercise, followed by a series of strength exercises designed to enhance muscular resistance and a creative dance training phase focused on motor problem-solving tasks.

The strength training will include exercises for both the upper (biceps curls, triceps extensions, rows, shoulder presses, chest presses, and lateral and front raises) and lower body (squats and their variations, deadlifts, forward and backward lunges, and hip thrusts) as well as abdominal work (crunches, Russian twists, oblique exercises, dead bugs, isometric and dynamic planks, and Pallof presses). Training volume will be regulated through the number of sets and repetitions, and intensity will be progressively increased by adjusting exercise difficulty. Exercises will primarily be performed using body weight, with elastic resistance bands (~5 kg resistance) incorporated intermittently as supplementary equipment. All sessions will be accompanied by background music (see Supplementary Material Table S1);The creative dance training: In this study, creative dance is defined as a structured movement-based intervention in which participants engage in guided improvisation, expressive movement, and continuous decision-making in response to internal and external cues. Essential components include (1) improvisation within predefined movement constraints, (2) active selection among multiple motor solutions, (3) perception–action coupling to respond to dynamic stimuli, and (4) expressive and exploratory movement rather than repetitive patterns. Creativity in the sessions is systematically induced through specific task instructions and variations, aiming to enhance motor adaptability and cognitive flexibility. The creative dance will consist of five main exercises, each with its corresponding variations. Two of them (Trajectories and Passing) will follow a fixed structural pattern while being adapted according to the daily objective and the specific element of creative dance being addressed. Two sessions will be dedicated to each dance component: body, weight, contact, space, time, and interaction [26]. Exercise intensity will be monitored through movement speed and task duration. All sessions will be accompanied by either background or directive music (see Supplementary Material Table S1). Supplementary Material Document S1 contains the detailed of information about the exercise and the entire exercise program itself.

### 2.9. Control of Training Intensity

After each training session, participants will complete the Visual Analog Scale (VAS), the Borg Rating of Perceived Exertion (Borg-RPE), and the Borg Category-Ratio 10 scale (Borg-CR10) questionnaires to evaluate perceived pain and exertion.

The strength training program will adhere to the training principles established by the American College of Sports Medicine (ACSM) and will employ a linear progressive model [27]. Training volume and repetitions will progressively increase across the six weeks; see Figure 2A:Week 1: Two sets of 6–8 repetitions;Week 2: Two sets of 8–10 repetitions;Week 3: Three sets of 8–10 repetitions;Week 4: Three sets of 10–15 repetitions;Week 5: Four sets of 10–15 repetitions;Week 6: Four sets of 12–18 repetitions.

Participants will be instructed to work within these ranges according to their physical condition and pain levels. Those unable to reach the prescribed repetitions due to FM symptoms or physical limitations will be encouraged to perform as many repetitions as possible with the aim of gradual improvement. Conversely, participants feeling well and without symptom flare-ups will be invited to perform up to 5–8 additional repetitions beyond the prescribed range.

The creative dance training program includes creative motor tasks, such as free or improvised movement, that are designed to promote multiple and original motor responses. Similar to the strength training program, it will follow ACSM guidelines and will adopt a linear progressive model [27]. Training intensity will be primarily regulated through walking speed, while spatial variation (i.e., reducing or expanding the movement area) will serve as an additional method to increase or decrease exercise difficulty (see Figure 2B).

Participants will receive a reference scale for walking speeds to be used throughout the intervention: 0 = stop; 1 = slow; 2 = comfortable walk; 3 = brisk walk; 4 = fast walk; and 5 = very fast walk.

Week 1: Mostly stationary exercises and 20 min of walking at an average speed of level 2;Week 2: A total of 20 min of walking at an average speed of level 3, and 10 min of semi-static activities;Week 3–4: A total of 20 min of walking at speeds between levels 3–5, plus 10 min of semi-static work;Week 5–6: A total of 30 min of walking at speeds between levels 3–5.

### 2.10. Adherence, Attendance, and Compliance

Adherence will be evaluated based on attendance and compliance. Attendance will be defined as the percentage of sessions attended by each participant, as recorded by the physical exercise trainer, relative to the total number of scheduled sessions over six weeks, with two sessions per week, totaling 12 sessions. Minor variations in the total number of sessions may occur due to holidays or logistical reasons during intervention phases or for individual participants. Compliance will be defined as the percentage of sessions completed in accordance with the intervention protocol, calculated as the number of sessions completed according to protocol divided by the number of sessions with valid data, expressed as a percentage. A session will be considered completed when the participant:(1) performs the full 60-min training session (30 min of strength training and 30 min of creative dance training) and (2) completes the three post-session questionnaires assessing pain and perceived exertion (both the short and long versions of the Borg Scale).

### 2.11. Safety and Adverse Events

Participant safety will be monitored continuously throughout the program by the physical exercise professionals, who will deliver the intervention. He/she will record any adverse events occurring during or immediately after each session. An adverse event will be defined as any unexpected medical occurrence, symptom, or injury arising during participation, regardless of whether it is deemed related to the intervention. Given the nature of the program, potential minor adverse events may include transient muscle soreness or fatigue.

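### The adverse-event recording rule is narrower than the protocol's own definition and has no route for control-arm events, so harms data will describe class-time events in exercisers only

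*Protocol article*

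**What the plan says.** All of the adverse-event text is in section 2.11 of the protocol article.

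- **Who watches:** "Participant safety will be monitored continuously throughout the program by the physical exercise professionals, who will deliver the intervention".
- **When events are recorded:** "He/she will record any adverse events occurring during or immediately after each session".
- **What counts:** "any unexpected medical occurrence, symptom, or injury arising during participation, regardless of whether it is deemed related to the intervention".
- **What is anticipated:** "potential minor adverse events may include transient muscle soreness or fatigue".

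Section 2.8 describes the exercise arm as attending "two group-based sessions per week, lasting 60 min, with a maximum of ten participants per group", "while those in the control group will continue their usual daily routines". Section 2.10 puts the programme at six weeks and 12 sessions. Section 2.2.2 plans 22 women per arm.

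**The concern.** The section fixes who records, when, and what counts, and the three do not fit together. The definition includes events unrelated to the intervention, so it reaches background illness and injury. The recording rule reaches only what a trainer sees in class or just afterwards.

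Two things are at stake. First, a report that followed this rule would show some events in exercisers and none in controls, whatever happened to the controls. Without the same ascertainment in both arms, events due to the programme cannot be separated from the ordinary course of fibromyalgia. Second, the exerciser count could be incomplete for anything that starts between classes.

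This matters because section 4.2 looks ahead to use of the programme in fibromyalgia care, which needs a credible account of harms. Section 2.9 also raises the strength work per exercise from two sets of 6–8 repetitions to four sets of 12–18: from 2 × 6 = 12 to 4 × 12 = 48 at the lower end, and from 2 × 8 = 16 to 4 × 18 = 72 at the upper end.

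**Working it through.** The protocol gives no adverse-event count or rate, so there is no figure to reproduce. The check sets the statements side by side.

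1. **Definition against window.** The definition covers "any unexpected medical occurrence, symptom, or injury arising during participation". The window is class time plus an interval just afterwards whose length is not given. If participation means being in the trial, an event starting between two classes meets the definition but falls outside the window.

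2. **Window against arms.** The recorders are the people delivering the classes. Controls have neither classes nor trainer contact in the text. By this route, recordable events in controls = 0, for 22 / (22 + 22) = 50% of the sample.

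3. **Definition against example.** An event must be *unexpected*, but soreness and fatigue are named beforehand as possible adverse events. Two trainers could reasonably log the same soreness differently.

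4. **Scale of direct observation.** Sessions run "over six weeks, with two sessions per week, totaling 12 sessions", at 60 minutes each (section 2.8).
   - Exercise arm: 12 × 1 h = 12 h, out of 6 × 7 × 24 = 1,008 h. 12 / 1,008 = 0.0119, about 1.2%, plus the undefined interval after class.
   - Control arm: 0 h.

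   These figures describe observation time only. They are not the share of events captured or lost.

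5. **Could other data fill the gap?**
   - The pain and exertion scales after each session (section 2.9) are completed by exercisers only, straight after class, to control training intensity.
   - The FIQR and EQ-5D-5L (section 2.12.1) cover symptoms and pain in both arms, but as efficacy outcomes.
   - Falls, injuries and pain level appear under sociodemographic information (section 2.12.2). Whether they are asked again at post-test is unclear.

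   None of these is linked to adverse-event recording.

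**The case against.** The strongest defence is that a journal article condenses a fuller protocol, and a control-arm harms form or between-visit questioning could sit there. That stands as a caution: no other route is *described*, which is weaker than saying none exists. It does not remove the point, because the article states a recorder, a window and a definition, and these conflict as written.

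A second defence reads participation as taking part in the classes. Definition and window would then agree, but controls would fall outside the definition altogether, so the arm asymmetry remains. Likewise, *unexpected* might qualify only the first item in the definition's list. That softens the clash with soreness and fatigue but leaves the wording open to two readings.

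Third, safety is said to be monitored continuously. That sentence names the same class-delivering staff, and the next one sets the window.

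Some stronger inferences are tempting, and the document does not support them:

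- **That delayed soreness and flares will be missed.** Section 2.11 names only soreness and fatigue. Flares appear in section 2.9 as a condition on extra repetitions, not as adverse events. Nothing in the document says when soreness appears, and a woman may mention a late event at her next class. The text supports *may be missed*.
- **That about 99% of events are lost.** Clock hours, including sleep, do not measure event capture.
- **That a planned analysis is invalid.** Adverse events are not a listed outcome, and section 2.13 plans no comparison of harms between arms.

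**Conclusion.** The point holds as a badly fixed recording rule. Followed as written, it yields harms data for class time in the exercise arm and none for the 22 controls. Events first appearing between classes are outside the window, and the treatment of anticipated soreness and fatigue is ambiguous. A safety statement could then describe class-time events in exercisers and nothing wider, and a zero in controls would be uninformative.

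The size in events is unknown, because the document gives no event rates. No efficacy estimate, test or sample-size figure is affected. The conclusion assumes that the route in section 2.11 is the one used and that controls have no sessions, as section 2.8 describes. It is worth correcting because the correction is cheap.

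**What to change.** 1. Reconcile the definition with the recording rule in section 2.11: remove *unexpected*, and have trainers also log events that women report since their last class.
2. At the existing post-intervention visit, give all women in both arms the same short adverse-event form covering the six weeks. Self-completion fits the questionnaires already scheduled in section 2.7 and helps to protect the evaluator blinding in section 2.5.
3. Base any between-arm statement on that common form only. Report trainer-logged events separately, labelled as exercise arm only.
4. If a fuller protocol already contains such a route, state it in section 2.11.

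The cost is one question at each class and one short form at a visit that takes place anyway. There are two downsides. Recall over six weeks is imperfect. Exercisers, who are unblinded, would also be asked up to 12 times before they complete the form, while controls would not, which may raise exercisers' later reporting. Both should be stated as limitations. The change touches no dose, schedule or clinical rule.

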## 1. Introduction

Fibromyalgia (FM) is a long-term rheumatic condition of unclear etiology that predominantly affects women. It is characterized by widespread musculoskeletal pain as well as reduced physical capacity, balance impairments, fatigue, depression, anxiety, and sleep disturbances [1]. Individuals with FM who present a high risk or fear of falling [2] tend to reduce their motor activities, generating a cycle of physical deterioration, decreased quality of life, loss of autonomy, and a greater degree of disability [3].

Physical exercise has been shown to reduce pain [4], symptom severity, and fatigue [5] as well as to improve quality of life, physical fitness, sleep [5], and psychological well-being [5]. Multicomponent programs that combine aerobic and strength exercises are particularly effective for decreasing pain and enhancing both physical and mental health. Other modalities, such as whole-body vibration [6], aquatic exercise [7] or virtual reality-based interventions, have also demonstrated benefits in functional capacity, along with a reduction in both the risk and fear of falling.

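### The adverse event definition requires an event to be unexpected, yet the next sentence names foreseen soreness and fatigue as adverse events; the two must be reconciled

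*Protocol article*

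**What the plan says.** Section 2.11 (Safety and Adverse Events) gives the only definition in the article: "An adverse event will be defined as any unexpected medical occurrence, symptom, or injury arising during participation". The same sentence adds that this holds "regardless of whether it is deemed related to the intervention", so relatedness is not a condition for counting. The sentence after it refers to the nature of the programme and states that "potential minor adverse events may include transient muscle soreness or fatigue". Recording is assigned to the exercise professional who delivers the sessions: "He/she will record any adverse events occurring during or immediately after each session".

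Three other places bear on what could happen in a session:

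- Section 2.9 (Control of Training Intensity) provides for "Those unable to reach the prescribed repetitions due to FM symptoms or physical limitations" and, in the other direction, says that "participants feeling well and without symptom flare-ups will be invited to perform up to" a stated number of extra repetitions. Both provisions concern training load; neither says how a flare-up is classified for safety.
- Section 2.8 (Intervention) describes exercises aimed at "promoting effective motor strategies to regain stability under dynamic and potentially destabilizing situations".
- The Introduction speaks of "Individuals with FM who present a high risk or fear of falling" as part of the background on this population.

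Section 2.9 also has participants complete a pain visual analogue scale (VAS) and two Borg exertion scales after each session. Section 2.10 makes these questionnaires a condition for a session to count as completed.

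**The concern.** Expectedness describes an event. It should not decide whether the event is recorded at all. Once it is a condition for being an adverse event, the recorder must first judge whether the occurrence was foreseeable, and in this trial the common harms are foreseeable. Fatigue is a feature of the disease, and the strength work in Section 2.9 rises from two sets of 6–8 repetitions to four sets of 12–18 over six weeks. A recorder could reasonably regard most soreness or fatigue as expected.

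What is at stake is the meaning of the adverse event count. If the definition is followed, foreseen minor harms are left out; if the example sentence is followed, they are included. A reader of the results could not tell which rule produced the number. The problem cannot be repaired at analysis, because an event that was never written down cannot be recovered.

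**Working it through.** No arithmetic applies: the protocol states no safety rate, threshold or target, so there is no figure to reproduce. The check is to set the two sentences of Section 2.11 beside each other and ask how each kind of event would be handled.

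| Event in or just after a session | Definition sentence, read literally | Example sentence | Result |
|---|---|---|---|
| Injury nobody anticipated | Counted | Not addressed | Counted |
| Transient muscle soreness | Not counted: foreseen from the programme | Named as an adverse event | Contradiction |
| Transient fatigue | Not counted: foreseen from the programme | Named as an adverse event | Contradiction |
| Fibromyalgia symptom flare-up | A symptom, counted only if judged unexpected | Not addressed | Left to the recorder |
| Fall without injury | Unclear whether it is a medical occurrence, and whether it is unexpected | Not addressed | Left to the recorder |

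1. **Soreness and fatigue.** The example sentence derives them from the nature of the programme. An event predicted on that ground is expected, so it does not meet the condition in the definition. The conflict arises from the wording alone and depends on no assumption about rates.
2. **Intent.** The definition sets relatedness aside, which points to broad capture. The condition of unexpectedness pulls the other way within the same sentence.
3. **Flare-ups.** Section 2.9 anticipates them when setting load, but nothing there or in Section 2.11 says whether one is an adverse event. An unanticipated flare-up could qualify as a symptom; a recorder who regards flare-ups as part of the disease could leave it out.
4. **Falls.** Section 2.8 puts women into potentially destabilising situations. No section says how a fall during a session is classified if no injury follows.
5. **Size.** The number of affected events would be the participant-sessions delivered, times the rate of foreseeable minor events, times the share of recorders' decisions that follow the literal definition. The documents give neither the rate nor the share, so the product cannot be calculated.

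**The case against.** The strongest reply is that Section 2.11 should be read as a whole. The paragraph does name soreness and fatigue as adverse events, so a sensible recorder would count them; the word *unexpected* may simply have been meant as *unwanted*. This stands in part. It is wrong to say that these harms are simply defined out, as a reader of the definition alone might infer. They are excluded by one sentence and included by the next. But a recording rule should not depend on the recorder choosing the right sentence, and if *unwanted* was meant, the correction proposed here says so.

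Second, post-session pain and exertion are collected by the VAS and Borg scales however an event is classified. This also stands: the information is not wholly lost. The scales are placed under training-intensity control, however. The article links no score to an adverse event, and the scales do not capture falls or injuries.

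Third, the article does not class flare-ups or falls without injury as expected harms. Flare-ups appear only in connection with load, the remark on falling is background, and the balance exercises train women to regain stability, so a fall could well be judged unexpected. This is correct. For these events the point is only that their status is open, not that they are excluded.

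Fourth, severity grades, event forms and tabulations are details that an article may leave to the full protocol. Agreed, and their absence is not raised. The point concerns a definition that the article does state.

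**Conclusion.** The point holds as an internal contradiction. Two consecutive sentences of Section 2.11 cannot both be applied literally, and foreseeable minor harms are counted or not depending on which is followed. The adverse event count may therefore be too low or inconsistent. The contradiction for soreness and fatigue rests on the stated wording alone; the open status of flare-ups and falls rests on reading Section 2.11 together with Sections 2.8 and 2.9.

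Three stronger readings are tempting and are not supported:

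- **That the safety result will look too favourable.** No tolerability objective, outcome or conclusion is stated. Recording is tied to sessions, which the control group does not have, so the direction of any distortion between the arms is not clear.
- **That counts will differ between associations.** The article does not say how trainers are allocated to associations or that they would read the paragraph differently.
- **That a number of missed events can be given.** Any figure would rest on an assumed event rate that nothing in the documents anchors.

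Safety is not a primary outcome, so this does not threaten the efficacy analysis. It is still worth correcting before events are recorded, because the loss is irreversible and the correction is small.

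**What to change.** In the definition in Section 2.11, replace *unexpected* with *untoward, whether or not expected*. Record expectedness as an attribute of each event, alongside relatedness, so that expected and unexpected events can be told apart afterwards. Add a short clause making clear that symptom flare-ups and falls during sessions fall under the definition. The sentence on soreness and fatigue can then stand as it is, since it will agree with the definition.

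This changes only how events are classified and recorded, not the exercise programme or its load rules. The cost is a one-sentence edit and an added field on the event record. The downside is a higher reported number of minor events, which the expectedness attribute allows a reader to interpret.
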